### Trial design

This is a single-blind, randomized controlled clinical trial with two parallel branches, EMDR and ST. Patients will be matched for age, sex, illness duration and number of affective episodes the year before the clinical trial. The primary outcome variables that are affective relapses, symptoms of trauma and cognition and psychosocial functioning, will be assessed at six time points; pretreatment (T0), mid-treatment at 2 weeks (T1) and at 3 months (T2), post treatment at 6 months (T3), and follow-up evaluations at 12 (T4) and 24 months (T5) (see Fig. 1). The secondary outcome variables that are the course and prognosis of the disease, will be assessed in follow-up evaluations at 12 (T4) and 24 months (T5). The research assistants conducting the clinical assessments will be blind to the participants’ research condition. Patients are not blind to treatment as it is impossible for a therapist to offer and for a patient to receive therapy without being aware of the techniques that they are using orreceiving. The study has been approved by the Ethics Committee of the Germanes Hospitalàries del Sagrat Cor de Jesús (reference number: PR-2014-15), the Hospital Clínic of Barcelona (reference number: HCB/2015/1005) and the Hospital del Mar (reference number: 2015/6502/l). All participants will sign informed consent prior to enrollment. Details of the trial design can be also gathered from Additional file 1 (Standard Protocol Items: Recommendations for Interventional Trials (SPIRIT) flow diagram) and the SPIRIT Checklist (Additional file 2).

**Fig. 1 Fig1:**
[figure not shown]
Flow diagram of enrollment, intervention and assessments. YMRS: Young Mania Rating Scale; BDRS: Bipolar Depression Rating Scale; CGI-BP-M: Clinical Global Impression, PTSD: Posttraumatic Stress Disorder; CAPS: Clinician Administered PTSD Scale; IES-R: Impact Event Scale; H-RLSI: The Holmes-Rahe Life Stress Inventory; SUD: Subjective Units of Distress; SCIP: Screen for Cognitive Impairment in Psychiatry; MSCEIT: The Mayer-Salovey-Caruso Emotional Intelligence Test; FAST:Functioning Assessment Short Test; CLQ-8: Client Satisfaction Questionnaire

### Participants

The patient sample will consist of 82 patients fulfilling *Diagnostic and Statistical Manual of Mental Disorders, fourth edition, text revision* (DSM-IV-TR) criteria for bipolar I and II disorder, based on clinical interview and review of case notes. Inclusion criteria will be: (1) age between 18 and 65 years, (2) presence of between two and six affective episodes in the last year, (3) current clinical status of euthymia upon clinical evaluation, defined as the presence of clinical remission (Bipolar Depression Rating Scale (BDRS) <8 and Young Mania Rating Scale (YMRS) <6; or subsyndromal status defined as BDRS ≥8 and <14 and/or YMRS ≥7 and <12), (4) presence of one or more traumatic events causing current trauma-related symptoms (The Holmes-Rahe Life Stress Inventory, H-RLSI >0; The Clinician-administered PTSD Scale (CAPS): frequency event >1, intensity of symptom >2; Impact of Event Scale-Revised, IES-R >0), and – following the standard EMDR protocol [19] – Subjective Units of Distress (SUD) >5 (range from 0 to 10, with a score of 10 meaning maximum stress).

Exclusion criteria will be: (1) substance abuse/dependency within 3 months prior to participation (except of nicotine abuse/dependency), (2) neurological disease or brain trauma history, (3) suicidal ideation, (4) previous involvement in trauma-focused therapy, (5) current psychotherapy during the study and months of follow-up.

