### Randomization procedure

All patients meeting the inclusion criteria receive the pretreatment (T0) assessment. After T0, participants will be assigned to EMDR or the ST group by two independent researchers using the following covariate-adaptive allocation procedure [26]: (1) the first two patients will be randomly allocated to EMDR or ST with *p* = 0.5, (2) the next patients will be allocated as follows: (b1) if one group already includes two more patients than the other group, the patient will be randomly allocate to EMDR or ST with *p* = 0.8 for the smallest group and *p* = 0.2 for the largest group, (b2) otherwise, we will first simulate that the patient is allocated to EMDR and calculate the sum of the between-group square standardized differences in age, sex, illness duration and number of affective episodes the year before the clinical trial between groups, we will then simulate that the patient is allocated to ST and recalculate the sum, and finally randomly allocate the patient to EMDR or ST with *p* = 0.8 for the group with the smallest sum and *p* = 0.2 for the group with the largest sum. For example, if we had already included 10 patients to the EMDR group and 8 patients to the ST group, the 19th patient would be randomly allocated with *p* = 0.2 for EMDR and *p* = 0.8 for ST. If they were allocated to ST, we would calculate the above sum of covariates after simulating that the 20th patient is allocated to EMDR and after simulating that is allocated to ST, and if the sum of the EMDR simulation was larger than the sum of the ST simulation, we would randomly allocate the 20th patient with *p* = 0.2 for EMDR and *p* = 0.8 for ST. Following this procedure, final groups should be balanced in size and matched in age, sex, duration and episodes. All steps of the randomization process will be automatically carried out in a central location using a computer program.

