### Dropouts and follow-up

In case of an affective relapse with admission to the hospital during the intervention phase of 6 months patients will be excluded from the trial and considered as dropouts. In case of relapse which requires an admission to the hospital during the follow-up, patients will be maintained in the trial to obtain maximum information on the course of the illness.

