## Statistical analysis

The baseline distribution of sociodemographic and clinical characteristics in each treatment arm will be reported using descriptive statistics.

The main hypothesis of the change in the time to relapse (in weeks) will be analyzed using Cox regressions, and the hypotheses of the changes in the scores of clinical scales as compared to baseline will be tested using repeated measures analyses of variance (ANOVAs) that will include time, treatment arm and their interaction. Those variables that show statistically significant between-arm differences at baseline will be added as covariates in the Cox regressions and repeated measures ANOVAs. For each of the analyses effect size measures (hazard ratio or Hedges’ *g*) will be estimated.

An intention-to-treat (ITT) analysis will be employed to provide unbiased comparisons among the treatment groups, using multiple imputations to deal with the losses of follow-up.

R software will be used to carry out the statistical analyses.

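### Entry sets no minimum interval since the last episode, and time since that episode is neither balanced at allocation nor adjusted for except by a baseline significance test

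*Protocol article*

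**What the plan says.** Under Participants, the article requires "presence of between two and six affective episodes in the last year". The next criterion reads "3) current clinical status of euthymia upon clinical evaluation, defined as the presence of clinical remission", with score limits on the BDRS and YMRS, and continues "or subsyndromal status defined as BDRS ≥8 and <14 and/or YMRS ≥7 and <12". A patient with residual symptoms can therefore enter. Neither criterion says how long that status must have lasted or how long ago the last episode must have ended.

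Under Randomization procedure, "All patients meeting the inclusion criteria receive the pretreatment (T0) assessment", and allocation follows T0. No stability period comes between. The variables balanced are given under Trial design: "Patients will be matched for age, sex, illness duration and number of affective episodes the year before the clinical trial". Time since the last episode is not among them.

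Under Statistical analysis, "The main hypothesis of the change in the time to relapse (in weeks) will be analyzed using Cox regressions". A baseline variable becomes a covariate there if it shows a statistically significant difference between arms.

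Three places bear on whether an early relapse counts:
- Trial design lists affective relapses among outcomes assessed at six time points, the first after baseline being at 2 weeks.
- Computation of sample size describes the dependent variable as relapse risk after treatment, with 24 months of follow-up.
- Dropouts and follow-up says that patients admitted for a relapse "during the intervention phase of 6 months patients will be excluded from the trial and considered as dropouts".

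**The concern.** Patients with several episodes in the past year may enter soon after the last one ended, some with residual symptoms. The Background itself associates subsyndromal symptoms with a higher risk of relapse. If such an episode returns within weeks and does not lead to admission, it can be scored as a relapse although little of the therapy has been delivered. The time-to-relapse outcome then mixes continuation of an old episode with new relapse.

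Two things are at stake. The first is dilution: events on which treatment has had little chance to act pull the hazard ratio towards 1 and cost power. The second is chance imbalance: a plausible predictor of early relapse is left out of the balancing in a small trial and is adjusted for only when a baseline test happens to be significant.

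**Working it through.** **Sessions delivered early.** 20 sessions in 6 months (26 weeks), at an even pace: 20/26 × 2 = 1.5 sessions by week 2.

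**The plan's own figure.** Computation of sample size gives 36 per group for a hazard ratio of 2, 80% power and alpha 0.005. With the Freedman-type form, events = ((2+1)/(2−1))² × (z_α + z_β)²:
- two-sided 0.005: 9 × (2.807 + 0.842)² gives 120 events, 60 per arm even if everyone relapses;
- two-sided 0.05: 9 × (1.960 + 0.842)² gives 71 events, 36 per arm if everyone relapses.

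The stated 36 is therefore reproduced at 0.05 but not at 0.005. That is a separate matter, and this point does not depend on it. Both levels are shown below.

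**Dilution, as illustration only.** The document gives no share of events that are continuations, so the share q is an assumption, as is a treatment effect of exactly nil on those events. Two approximations are used:
- A: q is the share of all first events, and the observed HR is 2^(1−q).
- B: q is the share of control-arm relapses, and the observed HR is 1/(q + (1−q) × 0.5).

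Power = Φ(ln(HR) × √72/2 − z_α), where 72 events is the most that the planned 72 completers can give (two-sided).

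| q | A: HR | A: power at 0.05 / 0.005 | B: HR | B: power at 0.05 / 0.005 |
|---|---|---|---|---|
| 0 | 2.00 | 84% / 55% | 2.00 | 84% / 55% |
| 10% | 1.87 | 75% / 44% | 1.82 | 72% / 39% |
| 20% | 1.74 | 65% / 33% | 1.67 | 58% / 26% |
| 30% | 1.62 | 54% / 23% | 1.54 | 45% / 16% |

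The table shows the direction and how sensitive power would be. It does not estimate the loss in this trial.

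**Imbalance that the covariate rule lets through.** The level of the baseline test is not stated; I assume 5%, two-sided. With 41 per arm, the standard error of a standardised mean difference is √(2/41) = 0.22 SD. The difference needed for significance is 1.99 × 0.22 = 0.44 SD. Treating allocation as simple randomisation for this variable, the rule would be triggered in about 5% of trials. A difference larger than one standard error (0.22 SD) would arise in about a third. Most such imbalances would pass unadjusted. The resulting shift in the log hazard ratio is roughly b × d, where d is the imbalance in SD and b the log hazard ratio per SD. The document gives no value for b.

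**The case against.** The strongest case on the other side is that much of the apparent harm has to be read into the text. A reader might infer four stronger things, none of which the article supports.

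- *Euthymia is judged at one visit.* The number of ratings is not stated. BDRS and YMRS are also scheduled at T0 (Table 1), so two ratings fit the text as well as one.
- *Every early return is scored as a relapse.* Relapses with admission in the first 6 months become dropouts, and the after-treatment wording leaves the start of the clock open. What remains is the non-admitted early return. The six-time-point statement under Trial design places it within the assessed outcome, so it can be counted; that it will be is not settled.
- *Therapy could not have prevented it.* This is a clinical assumption. Both arms contain work on warning signs from the start of the programme. The schedule supports only that little therapy had been delivered.
- *The early event rate sizes the problem.* Carrying forward 2 to 6 episodes a year at constant hazard, 1 − exp(−rate × weeks/52) gives 7–21% with an event within 2 weeks and 14–37% within 4. The Background figure of almost 70% relapsing in 2 to 4 years gives −ln(0.30)/4 to −ln(0.30)/2 = 0.30 to 0.60 a year, hence 1.2–2.3% and 2.3–4.5%. Both sets are ordinary incidence. A constant hazard has no early excess, so neither says what share of events are continuations.

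Two further arguments have weight. Subsyndromal patients appear to be admitted on purpose, since the pilot studied them, and requiring a longer well period would trade recruitment and generalisability for a cleaner endpoint. Also, the number of prior-year episodes is in the allocation sum and probably correlates with recency, so recency is not wholly left to chance. These arguments defeat a demand to change eligibility. They do not justify leaving adjustment for time since the last episode to a baseline significance test.

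**Conclusion.** The point holds in a limited form. The entry criteria state no minimum interval since the last episode, so some early non-admitted relapses can be continuations of it. The expected consequence is dilution of the hazard ratio towards 1 and some loss of power. Dilution alone does not favour either arm, and the document does not allow its size to be estimated. The table rests on an assumed share and an assumed nil effect.

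The firmer part is the handling of the predictor. Time since the last episode is outside the allocation sum, and imbalances up to about 0.44 SD (assuming a 5% test and 41 per arm) would go unadjusted in the primary model. That it predicts early relapse is plausible but not shown in the document. The change is worth making mainly because it is cheap and better than a significance-triggered rule.

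**What to change.** 1. Record at T0 the end date of the last affective episode. For patients already enrolled, recover it from the case notes that the article says are reviewed, without knowledge of arm or outcome.
2. Enter time since that date, on a log scale, as a prespecified covariate in the primary Cox model whatever its baseline difference.
3. Add a prespecified sensitivity analysis restricted to patients above a value of this variable that the investigators fix in advance. Because the variable predates randomisation, the comparison stays randomised.
4. State what the covariate does: it handles imbalance and improves precision. It does not separate continuation from new relapse, so the dilution remains in the primary estimate.
5. Reconcile Trial design, Computation of sample size, Dropouts and follow-up, and Statistical analysis on whether treatment-phase relapses count and from what date time to relapse is measured.

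The cost is one date on the CRF, one model term, and fewer events in the sensitivity analysis, which will be imprecise with about 41 per arm. No change to eligibility and no particular euthymic period is proposed.

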### Randomization procedure

All patients meeting the inclusion criteria receive the pretreatment (T0) assessment. After T0, participants will be assigned to EMDR or the ST group by two independent researchers using the following covariate-adaptive allocation procedure [26]: (1) the first two patients will be randomly allocated to EMDR or ST with *p* = 0.5, (2) the next patients will be allocated as follows: (b1) if one group already includes two more patients than the other group, the patient will be randomly allocate to EMDR or ST with *p* = 0.8 for the smallest group and *p* = 0.2 for the largest group, (b2) otherwise, we will first simulate that the patient is allocated to EMDR and calculate the sum of the between-group square standardized differences in age, sex, illness duration and number of affective episodes the year before the clinical trial between groups, we will then simulate that the patient is allocated to ST and recalculate the sum, and finally randomly allocate the patient to EMDR or ST with *p* = 0.8 for the group with the smallest sum and *p* = 0.2 for the group with the largest sum. For example, if we had already included 10 patients to the EMDR group and 8 patients to the ST group, the 19th patient would be randomly allocated with *p* = 0.2 for EMDR and *p* = 0.8 for ST. If they were allocated to ST, we would calculate the above sum of covariates after simulating that the 20th patient is allocated to EMDR and after simulating that is allocated to ST, and if the sum of the EMDR simulation was larger than the sum of the ST simulation, we would randomly allocate the 20th patient with *p* = 0.2 for EMDR and *p* = 0.8 for ST. Following this procedure, final groups should be balanced in size and matched in age, sex, duration and episodes. All steps of the randomization process will be automatically carried out in a central location using a computer program.

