## Background

Bipolar disorder (BD) is a serious neuropsychiatric condition of major public health importance with a complex multifactorial etiology, involving both genetic and environmental factors and associated with high mortality by suicide. BD is characterized by chronic instability of mood, circadian rhythm disturbances and continual fluctuations in energy levels, affect, sleep and cognitive appraisal of the self and others [1]. Although the disorder is conventionally characterized as being episodic in nature, with full recovery between periods of mania and depression, recent data suggest that many bipolar patients do not obtain a complete remission but continue to experience subsyndromal manic or depressive symptoms [2]. This is a clinically important issue since (1) subsyndromal symptoms are associated with a higher risk of relapses and poorer social functioning [3] and (2) interepisode affective instability seems to be refractory to pharmacological treatment [4]. Further possible risk factors for relapses include substance abuse, comorbid anxiety disorders, personality disorders or physical diseases [5].

The intervention strategies available for BD include essentially pharmacotherapy but also, increasingly, psychosocial interventions such as cognitive behavioral therapy, psychoeducation, interpersonal and social rhythm therapy, and family intervention [6]. However, despite the everyday use in clinical practice of both types of intervention, almost 70% of BD patients suffer from at least one affective relapse within 2 to 4 years [7–9].

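### Entry mood state, which the protocol itself links to relapse, is neither balanced at allocation nor adjusted for in the Cox model unless the arms differ significantly at baseline

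*Protocol article*

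**What the plan says.** - **Who enters.** Inclusion criterion 3 (Participants) requires "current clinical status of euthymia upon clinical evaluation, defined as the presence of clinical remission" (BDRS below 8 and YMRS below 6), but also accepts "subsyndromal status defined as BDRS ≥8 and <14 and/or YMRS ≥7 and <12". Two mood states are therefore eligible.
- **Why that matters for the outcome.** The Background states that "subsyndromal symptoms are associated with a higher risk of relapses and poorer social functioning". It gives no hazard ratio.
- **What is balanced.** Trial design: "Patients will be matched for age, sex, illness duration and number of affective episodes the year before the clinical trial". Randomization procedure: the covariate-adaptive rule uses the "sum of the between-group square standardized differences in age, sex, illness duration and number of affective episodes the year before the clinical trial". Both lists hold the same four factors, and neither includes mood state.
- **What is known at allocation.** The T0 assessment precedes allocation, and Table 1 schedules both YMRS and BDRS at T0.
- **What the analysis does.** "The main hypothesis of the change in the time to relapse (in weeks) will be analyzed using Cox regressions". Covariates enter by this rule: "Those variables that show statistically significant between-arm differences at baseline will be added as covariates in the Cox regressions and repeated measures ANOVAs". The Limitations section says pharmacological treatment will also be taken into account. Mood state is not mentioned.

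**The concern.** The protocol names a predictor of its main outcome, lets eligibility span both levels of it, and measures it before allocation, but then fixes two rules that together leave it uncontrolled in most cases. The allocation rule ignores it. The adjustment rule acts only when a baseline test is significant, which in a small trial means only when the imbalance is large. A baseline test between randomised arms asks whether chance produced the difference, and that is already known. It does not ask whether the variable predicts relapse, which is what decides whether adjusting helps.

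At stake are the precision and credibility of the relapse hazard ratio. A moderate surplus of subsyndromal patients in one arm would move the estimate in either direction, and the stated plan would not correct it. The covariate set of the main model would also depend on the baseline data instead of being fixed beforehand.

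**Working it through.** The protocol gives no figure for expected imbalance, so there is none to reproduce.

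**Inputs from the protocol** (Computation of sample size): 41 patients per arm recruited, 72 evaluable in total, hazard ratio 2, 24 months' follow-up. The Background reports almost 70% of patients relapsing within 2 to 4 years.

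**Assumptions, not in the protocol:** a subsyndromal share of 30-70%; a relapse hazard ratio for subsyndromal versus remitted of 2 (range 1.5-2.5); baseline tests at the two-sided 0.05 level; mood state unrelated to the four balanced factors.

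**1. When would the adjustment rule act?** At a 50% share, the smallest significant difference is about 1.96 × √(2 × 0.25 / 41) = 0.216. In whole patients (Pearson chi-square without continuity correction):

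| Subsyndromal, arm A v arm B (of 41 each) | Difference | p |
|---|---|---|
| 25 v 16 | 22 points | 0.047 |
| 25 v 17 | 20 points | 0.077 |
| 17 v 8 | 22 points | 0.031 |
| 16 v 8 | 20 points | 0.052 |

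A gap of nine patients is adjusted for; a gap of eight is not. Testing T0 scores instead of the two classes does not lower the bar: 1.96 × √(2/41) = 0.43 SD, the same standardised distance as 0.216/0.5.

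**2. How often do imbalances arise?** Exact calculation with two independent binomial counts of size 41:

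| Subsyndromal share | P(≥10 points) | of which not significant | P(≥15 points) | of which not significant |
|---|---|---|---|---|
| 30% or 70% | 0.28 | 0.23 | 0.12 | 0.07 |
| 50% | 0.32 | 0.26 | 0.15 | 0.09 |

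About four-fifths of imbalances of at least 10 points (0.23/0.28, 0.26/0.32), and more than half of those of at least 15 points, would go unadjusted.

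**3. Does the written allocation change this?** The published rule was simulated with 82 patients, 1,500 runs per setting and mood state independent of the four factors. It gave about 32% for ≥10 points and 14-16% for ≥15 points, much like simple randomisation. With mood state added as a fifth term, these fell to 2-3% and at most 0.3%.

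**4. What does a 15-point imbalance do to the estimate?** At a mean share of 50% the arms hold 57.5% and 42.5% subsyndromal patients. The ratio of average hazards due to mood state alone is (0.425 + 0.575 × 2) / (0.575 + 0.425 × 2) = 1.575/1.425 = 1.105, or 0.10 on the log scale.

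A large-sample unadjusted Cox calculation used a true hazard ratio of 2 and 80% relapse in the supportive-therapy arm by 24 months. This implies about 57% in the EMDR arm, so about 69% overall, close to the Background figure.

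| Mood-state HR | Balanced | 15 points, one direction | 15 points, other direction |
|---|---|---|---|
| 1.5 | 1.97 | 1.86 | 2.10 |
| 2 | 1.92 | 1.74 | 2.13 |
| 2.5 | 1.87 | 1.64 | 2.13 |

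Even with perfect balance, leaving out the predictor pulls the estimate slightly below 2.

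**5. How large is that against sampling error?** The standard error of the log hazard ratio is about 2/√events. With 72 events it is 2/√72 = 0.24; with 70% of 72 relapsing it is 2/√50.4 = 0.28. The shift is therefore 0.10/0.24 = 0.42 to 0.10/0.28 = 0.36 standard errors, roughly 0.4.

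**The case against.** The case on the other side is substantial, and much of it stands.

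- **Chance imbalance is not bias.** Allocation remains random, the test remains valid, and the standard error already carries this variation. A reader might infer from the figures above that the comparison is biased or the result invalid; the documents do not support that. This stands.
- **The choice of balancing factors is a judgement.** Trial design and Randomization procedure agree with each other, and nowhere does the protocol promise to balance mood state. The Background also names comorbid anxiety, personality disorders and physical disease as possible relapse risks, and no design balances everything. So the documents do not show that the allocation rule is wrong. Mood state does differ from those factors in defining eligibility and in being scored at T0.
- **Prior-year episode count is already balanced.** If it correlates with mood state, the imbalance probabilities above are upper-end figures. This stands; the protocol does not describe the correlation.
- **The sizes rest on assumptions.** Neither the subsyndromal share nor its hazard ratio is given, and the shift is moderate next to the planned hazard ratio of 2. This stands.
- **Large imbalances would be adjusted.** True, but only from about 22 points upward. This point does not rescue the rule, because the trigger depends on significance and not on prognostic value.

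A reader might also hope that balancing mood state would give an even split for reading the treatment effect by entry mood state. The protocol plans no such subgroup analysis, so that is no argument for a change.

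**Conclusion.** The point holds as a weakness of the stated adjustment rule, made more relevant by the absence of mood state from the allocation factors. The facts are in the protocol: mixed eligibility, a stated link to relapse, no balancing, and adjustment only on significance. Under an assumed 30-70% subsyndromal share, about 28-32% of trials of this size would show at least a 10-point imbalance and 12-15% at least 15 points, and most of these would go unadjusted. The consequence is moderate: with an assumed doubling of hazard, a 15-point imbalance moves an unadjusted estimate from about 1.9 to about 1.7 or 2.1, roughly 0.4 standard errors. It costs precision and credibility but not validity. The case for change rests mainly on how cheap the better rule is.

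**What to change.** In the Statistical analysis section, replace the significance-triggered rule for the relapse Cox model with a fixed covariate set: T0 BDRS score, T0 YMRS score, age, sex, illness duration and prior-year episode count, entered whatever the baseline tests show. Settle this before any comparison of the arms. Scores serve better than the two classes: they keep more information, and a YMRS of 6 with BDRS below 8 fits neither class as written under Participants, a gap that should be reconciled separately.

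The cost is small, since all these variables are collected before allocation. Six covariates plus treatment make seven coefficients, about 50/7 ≈ 7 events per coefficient if 70% of 72 patients relapse, so the model should be checked for stability. The reported hazard ratio becomes conditional on these covariates, and the report should say so.

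Optionally, if allocation is still open (recruitment began in July 2016), add the T0 scores to the allocation sum for later patients, with earlier patients counted in the running sum. This takes a short amendment and a program change. Balance on the other four factors becomes slightly looser; the 0.8/0.2 probabilities stay as they are. The fixed covariates are worth having even if this step is not taken.

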## Methods/design

This multicenter collaborative project will involve the participation of three different centers from the Barcelona catchment area, Spain (Hospital Benito Menni, Hospital Clinic of Barcelona and Hospital del Mar). EMDR and supportive therapy (ST) therapists have extensive experience in the application of both psychotherapies. EMDR therapists have already participated in the pilot study [24] and all therapists received a detailed day training in applying the EMDR therapy protocol and a well-defined ST program. The application of all clinical assessments has been defined and practiced within all participating raters. All centers and research groups involved have wide ambulatory facilities and outpatient clinics for BD patients that will facilitate meeting the recruitment criteria and development of this project.

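### The allocation rule, written out in full, leaves out centre in a three-hospital trial of 82 patients, and no model prespecifies centre; the cost is avoidable chance imbalance and some precision

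*Protocol article*

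**What the plan says.** Methods/design states that the project involves "the participation of three different centers from the Barcelona catchment area, Spain". Trial design lists the matching factors: "Patients will be matched for age, sex, illness duration and number of affective episodes the year before the clinical trial".

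Randomization procedure then gives the whole algorithm, with a worked example. The first two patients are allocated at 0.5. After that, if one arm is ahead by two, the smaller arm gets probability 0.8. Otherwise (branch b2) the arm giving the smaller sum of "between-group square standardized differences in age, sex, illness duration and number of affective episodes the year before the clinical trial" gets 0.8. The stated aim is that "final groups should be balanced in size and matched in age, sex, duration and episodes". The process is "automatically carried out in a central location using a computer program", and no separate list per hospital is described.

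In Statistical analysis, the scale outcomes use "repeated measures analyses of variance (ANOVAs) that will include time, treatment arm and their interaction", and time to relapse uses Cox regression with no fixed covariate named. Variables that differ significantly between arms at baseline are added to both. Limitations adds that drug treatment will be taken into account. Centre is named in none of these places.

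**The concern.** The trial uses covariate-adaptive allocation, which makes sense only if chance imbalance at this sample size is thought worth preventing. Centre is an obvious candidate for such control. Both arms are psychotherapies delivered by therapists, most outcomes are clinician-rated, and under Dropouts and follow-up a relapse with admission in the first six months removes the patient from the trial. Local practice could affect each of these, although the article does not say that it differs between the hospitals.

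Because the algorithm is complete as written, the absence of centre is a design choice and not a detail left to another document. If one hospital happens to supply more of one arm, its relapse rate carries into the observed treatment difference. Even with good balance, leaving a prognostic centre out of the models gives up some precision.

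**Working it through.** **Inputs from the protocol article.** 82 patients, 41 per arm, target hazard ratio 2 (Computation of sample size); the allocation rule above (Randomization procedure); three hospitals (Methods/design). The plan states no figure for centre balance, so there is none to reproduce.

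**Assumptions.** Site shares and covariate distributions, neither of which is given; site is unrelated to the four covariates.

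**1. Imbalance under the stated rule, by simulation.** Chance that at least one hospital splits 2:1 or worse:

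| Site shares (%) | Rule as written | Two centre indicators added to the sum |
|---|---|---|
| 33/33/33 | 11% | 0.4% |
| 50/30/20 | 22% | 5% |
| 60/25/15 | 34% | 11% |

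Repeat runs of 1,000 to 1,500 trials gave 12-13%, 22-23% and 34-37% for the middle column. That is in line with Monte Carlo error: √(0.34 × 0.66 / 1,000) = 0.015. A given hospital's share of patients differs between arms with an SD of 10 to 11 percentage points, and by more than 15 points in 14-17% of trials.

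A second run used a 65:35 threshold and one indicator for each of the three hospitals:

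| Site shares (%) | Some hospital worse than 65:35, as written | With centre | Largest within-hospital arm difference, median (95th percentile), as written | With centre |
|---|---|---|---|---|
| 33/33/33 | 16% | 0.3% | 5 (10) patients | 2 (4) |
| 50/30/20 | 26% | 1.5% | 5 (10) | 2 (4) |
| 60/30/10 | 46% | 14% | 4 (9) | 2 (4) |

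At 50/30/20, three indicators leave fewer bad splits (1.5%) than two do (5%), although 65:35 is the easier threshold to exceed. With two indicators, the hospital without its own indicator, here the smallest, is balanced only indirectly.

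**2. Would the baseline-significance rule bring centre in?** A chi-square test of centre by arm is significant at 0.05 in 4.5-4.9% of simulated trials. Example: hospitals of 27, 27 and 28 patients split 18:9, 11:16 and 12:16 (41:41 overall). Expected counts are 13.5, 13.5 and 14 per arm, so

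χ² = 2 × (4.5²/13.5 + 2.5²/13.5 + 2²/14) = 3.00 + 0.93 + 0.57 = 4.50 on 2 df, p = exp(−4.50/2) = 0.11.

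A clear 2:1 split in a third of the trial would not trigger adjustment.

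**3. Effect on the primary result.** To first order, shift in log HR = ln(hazard ratio of that hospital) × between-arm difference in its share. With an assumed hazard ratio of 1.5, ln 1.5 = 0.405.
- Typical: 0.405 × 0.10 to 0.11 = 0.041 to 0.045 (one SD). The simulated mean is about 0 and 95% of shifts lie within about 0.09.
- Example above: 18/41 − 9/41 = 0.22; 0.405 × 0.22 = 0.089, a factor of exp(0.089) = 1.09 on the hazard ratio.
- For scale: the standard error with 72 events is 2/√72 = 0.24, and the target is ln 2 = 0.69.

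**4. Error rate and power.** A further simulation assumed a baseline hazard of 0.7 per year, 24 months, two-sided 0.05 (not the planned 0.005) and no dropout, with 4,000 trials per setting. Ignoring centre throughout gave type I error of 4.6-5.8%. Putting centre in the sum and stratifying the test changed power at HR 2 by −0.5 to +2 points if one hospital has 1.5 times the hazard, and by +2 to +4 points if it has twice the hazard.

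**The case against.** The strongest reply is that this barely affects the result. Allocation is central, random and blind to hospital; type I error is not materially inflated, and the power gain is a few points at most. That stands, and it limits the size of the point.

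A reader might infer that treatment is confounded with site. The documents do not support this: imbalance arises only by chance, its expected effect is zero, and a hospital with patients in only one arm occurs in 0% to 2.5% of simulated trials.

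A reader might also infer that each hospital has its own therapists and raters with their own habits. The article does not say so. Methods/design describes common therapist training and assessments practised across all raters, Trial design keeps assessors blind, and the EMDR section has an external expert check recorded sessions. These reduce possible site differences but do not balance the arms within hospitals.

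Nor does the article exclude centre from the models. It is a condensed account, a fuller covariate list may sit in an analysis plan that is not shown, and the baseline rule could admit centre. So the modelling half of the point is that no prespecified centre term is visible and that the one stated route rarely operates. The allocation half does not depend on unseen documents.

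Finally, the imbalance figures depend on assumed site sizes and are driven by the smallest hospital: 15% of 82 is about 12 patients, where 2:1 means 8 against 4.

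**Conclusion.** The point holds as an avoidable weakness in efficiency and balance, not as a threat to validity. The rule omits centre. Some hospital is split 2:1 or worse in about 11-34% of trials over the assumed shares, and the stated covariate rule would correct for centre in only about 1 trial in 20. With one hospital at 1.5 times the hazard, the resulting shift in the log hazard ratio has an SD of 0.04 to 0.05, roughly a fifth of the standard error (0.045/0.24 = 0.19). A stronger centre effect would make it larger in proportion.

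The direction of these results does not depend on the assumptions; the percentages do, because the document gives neither site sizes nor centre differences. The change is worth making because it is inexpensive and follows the trial's own reason for adaptive allocation.

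**What to change.** 1. **Allocation, by protocol amendment.** Add centre to the b2 sum for the remaining patients, using one indicator per hospital, standardised like the other factors and computed over all allocations already made.
2. **Analysis, whether or not allocation is changed.** State that the primary Cox regression is stratified by centre or adjusted for it, and that centre is a fixed term in the models for the scale outcomes, in each case regardless of any baseline test. Fix this before outcome data are examined by arm.

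**Cost.** The first step needs a change to the allocation program and an amendment during recruitment (which began in July 2016) at a trial with three ethics approvals. It slightly loosens balance on the other four factors and does not remove imbalance in a very small hospital (14% worse than 65:35 remains at 60/30/10). The second step needs a sentence or two in the analysis section. Neither needs extra patients or visits. If the amendment is judged not worth making mid-trial, the second step alone still ensures that centre is accounted for.
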